**Fig. 3 Fig3:**
[figure not shown]
PrEP pathway in randomization arms. AGYW, adolescent girls and young women; HIV, human immunodeficiency virus; PrEP, pre-exposure prophylaxis [23]

Pharmacies randomized to the nurse navigator model receive tailored support counseling in addition to standard PrEP services. Support counseling by nurse navigators provides educational messaging tailored to AGYW and actionable advice targeting PrEP persistence and adherence and/or FP topics and addresses participants’ questions related to the content at each study visit. Counseling includes adherence encouragement (IMB domain: motivation), PrEP efficacy and safety (IMB domain: information), self-efficacy for prevention of HIV, support for potential PrEP side effects, behavioral skills (tips for remembering PrEP medications, IMB domain: behavioral skills), and strategies for remembering PrEP refill schedules (Fig. 1). All participants receive PrEP adherence counseling per Kenyan national guidelines.

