### Outcomes 

Our primary outcome is PrEP initiation among AGYW seeking contraception at retail pharmacies at enrollment and evidence of self-reported use at 1-month post-use (Table 1). Our second primary outcome is PrEP persistence at 10 months among AGYW who initiated PrEP. Our third primary outcome will be PrEP adherence defined as either TFV or DPV hair levels (depending on PrEP method) at 10 months.

**Table 1 Tab1:** Primary, secondary, and exploratory outcomes of the trial

Outcome		Definition
Primary	PrEP initiation	Binary endpoints (yes, no) of self-reported use of oral PrEP or DPV-VR at 1 month after acceptance at enrollment. Self-reported PrEP use will be considered initiation. If a participant declined or reported not using PrEP after acceptance, the participant will be considered non-initiated
	PrEP persistence	Binary endpoints (yes, no) of self-reported use of oral PrEP or DPV-VR at 10-month after acceptance at enrollment. Self-reported PrEP use will be considered persistence. If a participant declined PrEP or reported not using PrEP after acceptance or discontinued PrEP before 10 months will be considered non-persistent [24]
	PrEP adherence	Binary endpoints (yes, no) of detectable TDF levels in hair > 0.038 ng/mg or DPV levels > 0.0248 n/mg at 10-month visit will be considered adherent. If a participant stopped PrEP use or exited study before 10 months (i.e., no hair sample collected), the participant will be considered non-adherent
Secondary	PrEP method selection	Binary endpoints (yes, no) of self-reported DPV-VR compared to daily PrEP when offered at enrollment
	Predictors of non-adherence	Factors associated with poor adherence (< 90% adherent on PrEP or discontinuation) will include demographics, relationship/partner characteristics, psychosocial factors, socio-economic status, low health/HIV literacy, fear of disclosure
	STI incidence and cofactors	Frequency of STI (syphilis, gonorrhea, and chlamydia) detection at follow-up will be compared between randomization arms
Exploratory	HIV incidence	Frequency of HIV diagnosis at follow-up visits will be compared between randomization arms
	Quality of care	Binary endpoints (yes, no) based on MEASURE Evaluations indicators for quality of care in family planning (e.g., Did the provider ask if you were having a problem with your FP method?)
	Contraceptive method mix	Binary endpoints (yes, no) or LARC use will be compared between randomization arms and distribution of contraceptive method types

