### Recruitment 

AGYW who purchase a contraceptive method at a retail pharmacy study site will be recruited and enrolled. AGYW will be recruited into this trial following the purchase of contraception. Pharmacy staff will be aware of the study and asked to identify potentially eligible women at the point of contraceptive purchase. Pharmacy staff will explain the study to women who are potentially eligible and, if the woman expresses an interest in participating, will refer her to study staff. The study staff will then provide an in-depth explanation of the purpose and procedures of the study, in the language of the woman’s choosing, answer any questions the woman may have, and invite the woman to participate in the study. Participants will be informed that their participation is voluntary and that participation or nonparticipation in the study will in no way alter the nature of services that they receive at the pharmacy. If interested in participating, the study staff will screen the woman for eligibility, and, if eligible, the woman will provide written consent for their enrollment.

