## Data collection and management

### Plans for assessment and collection of outcomes 

We will collect baseline data on demographic and behavioral characteristics, contraceptive history, education, marital status, income, relationship characteristics, HIV status and testing results, and clinical characteristics. At each visit, study staff will administer questionnaires to participants to assess sexual behavior, PrEP attitudes, use, and adherence. We will also measure IMB model-guided psychosocial moderating factors, including experience of IPV, symptoms of depression, socioeconomic status (SES), sexual and reproductive empowerment (SRE) and health, and PrEP use disclosure. We will assess SRE with the SRE-Kenya scale, which has been adapted and validated by our group for Kenyan AGYW. We will also capture PrEP-related side effects (e.g., nausea, headaches, dizziness) [27]. Fidelity will be monitored through QA/QC with direct observation of client-provider interactions using MEASURE Evaluation’s framework for monitoring quality of care in family planning services [28]. Hair samples (~ 50 strands) will be collected from all participants at every follow-up visit to objectively assess PrEP use and longitudinal analyses of PrEP use patterns.

HIV testing will be conducted at every visit per national guidelines. In a subset of four pharmacies, two from each study arm, we will conduct STI (for gonorrhea and chlamydia). The study utilizes the Cepheid Gene X-pert machine, a 4-module NAAT analyzer for real-time PCR testing of CT/NG and TV assays with expedited partner treatment for those with STI diagnoses to allow for analyses of STI incidence by arm.

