## Statistical methods

### Statistical methods for primary and secondary outcomes 

We will conduct an intention-to-treat analysis with the primary exposure of randomization arm (pharmacy-based PrEP delivery with nurse navigators vs. standard pharmacy-based PrEP delivery without nurse navigators) to test the hypotheses that incorporating nurse navigators within a pharmacy-based PrEP delivery model will improve PrEP initiation, persistence, and adherence among AGYW seeking contraception at retail pharmacies.

For analyses of our primary outcomes, we will use a log-binomial regression model to estimate relative risks and 95% CI. We will include any imbalanced baseline demographic, clinical, or behavioral characteristics between arms as independent variables in an adjusted model. If primary outcome data are missing or in cases of loss to follow-up, we will assume PrEP discontinuation/nonadherence to fit the most conservative models.

Secondary outcome analyses will include PrEP method selection, predictors of non-adherence, and STI incidence and cofactors. For data analysis approaches, we will use log-binomial regression with robust standard errors for the former two and Anderson-Gill survival analysis for the later. Exploratory analyses will include HIV incidence, quality of care, and contraceptive method mixed by randomization arms (Table 1). We will use survival analysis, generalized estimating equation models with logistic link, and robust standard errors and log binomial regression respectively.

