## Discussion

Our results will have implications for other settings considering pharmacy-based PrEP delivery approaches for AGYW and will prime pharmacies to deliver novel PrEP agents in the pipeline (e.g., long-acting injectables and multi-purpose technologies). The study will inform nurse navigator approach for enhancing PrEP outcomes among AGYW and ultimately reducing HIV incidence in this important population disproportionately affected by HIV. Our study will advance PrEP implementation for AGYW and contribute insights on PrEP adherence and biomarkers (e.g., DPV-VR hair levels) that apply more broadly. In a subset of pharmacies, we will conduct STI (gonorrhea and chlamydia) screening and treatment including expedited partner treatment for those with STI diagnoses. This will be the first study to evaluate STI incidence among AGYW PrEP users in pharmacy setting, a population in which STIs have important implications, which can guide STI screening and treatment guidelines AGYW accessing PrEP outside of health facilities. If our nurse navigator approach positively affects non-HIV outcomes (e.g., increased access to desired contraceptive methods and counseling, sexual and reproductive empowerment), it could be readily integrated into other platforms (such as youth-friendly health clinics) aiming to improve SRH among AGYW.

In summary, the AGYW PrEP Pharmacy study may identify important information to guide the models for PrEP delivery which will benefit individuals in Kenya and other African countries with high HIV burden. The study will inform the policy to advance and incorporate community-based PrEP approaches for AGYW and ultimately contribute to minimizing the burden of HIV among AGYW in Kenya.

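### Exploratory LARC comparison names no visit and has no term for the method held at entry; the main cost is precision (minor)

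*Protocol article*

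**What the plan says.** Table 1 (Outcomes) lists contraceptive method mix as exploratory: "Binary endpoints (yes, no) or LARC use will be compared between randomization arms and distribution of contraceptive method types". The row gives no visit, whereas the STI and HIV rows both refer to follow-up.

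On timing, Recruitment says "AGYW will be recruited into this trial following the purchase of contraception". Implants are among the qualifying methods (Eligibility criteria) and among those the selected pharmacies provide (Study setting), so some women can already be LARC users when they join.

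In the navigator arm, counselling includes "actionable advice targeting PrEP persistence and adherence and/or FP topics" (Intervention description), so a change of method after entry is a plausible effect.

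On data, Plans for assessment and collection of outcomes states "We will collect baseline data on demographic and behavioral characteristics, contraceptive history, education, marital status, income, relationship characteristics".

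On analysis, the methods section takes HIV incidence, quality of care and method mix in that order, then says "We will use survival analysis, generalized estimating equation models with logistic link, and robust standard errors and log binomial regression respectively". Method mix therefore gets log-binomial regression. The only covariate rule is "We will include any imbalanced baseline demographic, clinical, or behavioral characteristics between arms as independent variables in an adjusted model". It stands in the paragraph on primary outcomes and depends on an imbalance being seen.

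**The concern.** What a woman uses later depends heavily on what she used at entry, above all for a long-acting method. Entry use precedes the intervention and is a measure of the same outcome, so it is the natural covariate. The stated analysis does not use it, and three things follow.

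- Variation in entry LARC use, between women and between pharmacies, stays in the error of the arm comparison. With 20 pharmacies this can widen the interval considerably.
- Allocation was restricted on AGYW purchase volume within sub-county, not on method mix. Pharmacy staff drew their own assignment (Sequence generation) and then identify potential participants (Recruitment). If they recruited differently by arm, the entry difference would pass into the unadjusted result.
- With no visit named, the purchase made before enrolment could itself be counted as outcome, although counselling cannot have influenced it.

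**Working it through.** **The plan's own figure.** None is given for LARC use. The only power statement in Sample size concerns PrEP persistence and has no bearing here.

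**Inputs from the protocol.** 10 pharmacies per arm; 95 women each less 15% attrition, so m = 0.85 × 95 ≈ 81. For the between-pharmacy coefficient of variation k, Sample size assumes 0.05 for persistence and gives 0.15 to 0.5 as typical for rare binary outcomes. I use 0.05 to 0.5.

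**Assumed inputs (not in the documents).** Entry LARC share p = 15% or 30%; 85% of LARC users continue; 5% of the others take it up; no navigator effect. Follow-up LARC share is then q = 0.05 + 0.80p, which is 17% for p = 15%.

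**Step 1, chance difference in entry LARC between arms.** SD = √{(2/10)[p(1−p)/m + (kp)²]}. For p = 0.15:
- k = 0.05: √{0.2 × (0.001574 + 0.000056)} = 0.018, or 1.8 points
- k = 0.5: √{0.2 × (0.001574 + 0.005625)} = 0.038, or 3.8 points

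**Step 2, follow-up difference without the entry term.** With v = (0.80kp)², SD = √{0.2 × [(q(1−q) − v)/m + v]}. For p = 0.15:
- k = 0.05: v = 0.000036, giving 1.9 points
- k = 0.5: v = 0.0036, giving 3.3 points

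**Step 3, with the entry term.** What remains is variation in continuation and uptake: √{0.2 × [p × 0.85 × 0.15 + (1−p) × 0.05 × 0.95]/m} = √{0.2 × 0.0595/81} = 0.0121, or 1.2 points. Estimating the slope adds a little.

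**Step 4, simulation** (2,000 runs per setting, analysed on pharmacy proportions, so clustering is respected):

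| Entry LARC | k | SD unadjusted (points) | SD adjusted (points) | Type I error, unadjusted / adjusted |
|---|---|---|---|---|
| 15% | 0.05 | 1.95 | 1.26 | 5.6% / 5.1% |
| 15% | 0.25 | 2.30 | 1.24 | 5.3% / 5.2% |
| 15% | 0.5 | 3.25 | 1.25 | 5.3% / 4.7% |
| 30% | 0.05 | 2.31 | 1.36 | 4.9% / 4.6% |
| 30% | 0.25 | 3.49 | 1.35 | 4.8% / 4.8% |
| 30% | 0.5 | 5.78 | 1.34 | 4.7% / 4.5% |

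At 15% entry LARC the SD falls by 35% (1 − 1.26/1.95) to about 61% (1 − 1.25/3.25). Type I error is about 5% either way.

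**Step 5, rare LARC at entry.** With 1-3% on LARC at entry, 85% continuing, 6% uptake and a between-pharmacy SD of 0.15 to 0.3 on the logit scale, the reduction is only about 2-12% (for example 1.24 to 1.21 points at 1%).

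**Step 6, a systematic enrolment difference.** Suppose recruitment made entry LARC 5 points higher in one arm. The unadjusted comparison then shows 0.80 × 5 = 4 points with no navigator effect, and rejects in 11% to 50% of runs across the settings in the table. The adjusted comparison shows about 0 and rejects in about 4% to 6%.

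**The case against.** The strongest reply is that this is an omission, not an error. A journal article names a model family for one of three exploratory outcomes; covariates may be set in the full protocol or analysis plan, which are not shown. The text does not say that the method at entry will be ignored, and the imbalance rule could be read to cover it. This limits the weight. It does not remove the point: the article does name the comparison and the model, and adding a recorded pre-intervention measure of the same outcome is a concrete improvement. A rule triggered by observed imbalance does not secure the precision gain.

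A reader might infer three stronger things that the documents do not support.
- *That chance imbalance biases the result.* It does not. Under randomization it is sampling variation, and Step 4 shows type I error at about 5% without adjustment when clustering is respected. A false effect on average needs differential recruitment. Unblinded staff make that possible; nothing shows that it occurs.
- *That the outcome is LARC use at month 10.* Table 1 names no visit, so any visit is the reader's own.
- *That a rollout decision hangs on this comparison.* The Discussion offers "increased access to desired contraceptive methods and counseling" as an example in a conditional remark. It does not mention LARC and sets no rule.

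The size also rests wholly on assumed rates. Larger gains than those in Step 4 can be produced, but with a logit SD of 0.9 at 15% entry LARC, k is about 0.74, above the protocol's own typical range. Finally, contraceptive history is said to be collected, but the article does not spell out that the method just bought is a recorded field. That should be confirmed.

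**Conclusion.** The point stands as a minor one on an exploratory outcome. The LARC comparison lacks a visit and, as stated, has no term for a method acquired before recruitment and navigator contact. The main consequence is lost precision: under the 15% scenario, an SD of 2.0-3.3 points where about 1.3 is attainable, and little gain if LARC at entry is as rare as 1-3%. The secondary consequence is exposure to differential recruitment, which is possible in this design but not shown. It is not a finding of bias or of inflated type I error, provided the analysis allows for clustering by pharmacy.

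**What to change.** In Table 1 and the statistical methods section:

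1. Define the outcome as LARC use at a named follow-up visit, for example month 10, and state that the enrolment purchase does not count towards it.
2. Pre-specify the woman's LARC use at enrolment as a covariate, whether or not an imbalance is seen.
3. State that standard errors allow for clustering by pharmacy. The list of exploratory methods leaves it unclear whether robust errors apply to the log-binomial model.
4. Name a fallback, such as modified Poisson regression, in case the log-binomial model does not converge. That is a practical risk when entry users and non-users differ as sharply as assumed here.
5. Show LARC uptake among women not on LARC at entry as a supporting result.

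A term for each pharmacy's share of LARC users at enrolment is optional and costs about one cluster-level degree of freedom.

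The cost is a few lines of wording, fixed before arm-level data are seen. No new data are needed if the method held at enrolment is recorded under contraceptive history.

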### Participant timeline 

Following written informed consent for participation, AGYW will be enrolled. Enrollment will include a detailed questionnaire, including assessment of demographic and behavioral characteristics, contraceptive history, education, marital status, income, relationship characteristics, HIV status and testing results, and clinical characteristics. Participants will be followed for 10 months, and study visits will be aligned with standard PrEP follow-up visits per national guidelines (i.e., first visit 30 days after PrEP acceptance, then every 3 months) for a total of 4 follow-up visits.

### Sample size 

To account for between-cluster variability, sample size calculations incorporated the coefficient of variation between pharmacies (*k*) [25, 26]. Assuming each cluster enrolls 95 (accounting for 15% attrition) AGYW and that 30% of participants achieve the primary outcome of PrEP persistence at 10 months (31) in the standard pharmacy PrEP model arm (control arm) arm with a coefficient of variation between clinics (*k*) of 0.05, 10 clusters per arm will give 90% power to detect a 15% absolute difference in proportions and a two-sided test with *α* = 0.05. Typical (*k*) values are 0.15 to 0.5 for rare binary outcomes and 0 to 0.05 for non-rare outcomes [25, 26]. Assuming 15% attrition, will enroll a final sample of 1900 ANC attendees at 20 sites (95 women per site; 950 women per arm).

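### The Sample size section's inputs and its stated power do not agree: k = 0.05 gives power above 99.9%, and 90% corresponds to k of about 0.22

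*Protocol article*

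**What the plan says.** All the inputs stand in the Sample size section of the protocol article. The calculation is built on the coefficient of variation between pharmacies, k. It takes 95 women enrolled per pharmacy with 15% attrition, and assumes that "30% of participants achieve the primary outcome of PrEP persistence at 10 months" in the control arm, with a "coefficient of variation between clinics (*k*) of 0.05" and "a two-sided test with *α* = 0.05". From these it concludes that "10 clusters per arm will give 90% power to detect a 15% absolute difference in proportions". It adds that typical k "values are 0.15 to 0.5 for rare binary outcomes and 0 to 0.05 for non-rare outcomes".

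The direction of the effect comes from the section on statistical methods for primary and secondary outcomes, where the hypothesis is that "incorporating nurse navigators within a pharmacy-based PrEP delivery model will improve PrEP initiation, persistence, and adherence". The comparison is therefore 30% v 45%. The same section sets the rule for missing outcomes: "If primary outcome data are missing or in cases of loss to follow-up, we will assume PrEP discontinuation/nonadherence".

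**The concern.** A k of 0.05 is very small for a 30% outcome. It means a between-pharmacy standard deviation of 0.05 × 30% = 1.5 points, so true pharmacy rates lie within about 3 points either side of 30% (±2 SD). With so little variation, 10 clusters per arm of 80 to 95 women should detect a 15-point difference almost with certainty, so a stated power of exactly 90% looks out of place.

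Power in this design depends strongly on k. If k and the power do not belong together, a reader cannot tell how much between-pharmacy variation the trial can absorb before power falls below the stated level.

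**Working it through.** **Inputs.** c = 10 pharmacies per arm; p0 = 0.30; p1 = 0.45; k = 0.05; two-sided alpha 0.05 (z = 1.96); 90% power (z = 1.2816). Cluster size m is taken as 95 (all women enrolled) and as 95 × 0.85 = 80.75, or about 81 (after attrition), because the text can be read either way. Under the missing-data rule, all 95 stay in the denominator.

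**Formula.** The article names k but does not print the formula. I assume the usual one for unmatched clusters:

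c = 1 + (1.96 + 1.2816)² × V / (p1 − p0)², with V = [p0(1−p0) + p1(1−p1)]/m + k²(p0² + p1²).

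Here p0(1−p0) + p1(1−p1) = 0.21 + 0.2475 = 0.4575; p0² + p1² = 0.09 + 0.2025 = 0.2925; (p1 − p0)² = 0.0225; (1.96 + 1.2816)² = 10.51.

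**Attempt to reproduce 90% at k = 0.05.**
- m = 81: V = 0.4575/81 + 0.0025 × 0.2925 = 0.00565 + 0.00073 = 0.00638. Power = Φ(√(9 × 0.0225/0.00638) − 1.96) = Φ(3.67) = 99.99%.
- m = 95: V = 0.00482 + 0.00073 = 0.00555. Power = Φ(6.04 − 1.96) = Φ(4.08) = 99.998%.

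The 90% is not reproduced. A noncentral t version with 18 degrees of freedom gives 99.99% and 99.997%. A beta-binomial simulation with a cluster-level t test gives about 100%.

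**Clusters needed for 90% at k = 0.05.**
- m = 81: c = 1 + 10.51 × 0.00638/0.0225 = 3.98.
- m = 95: c = 1 + 10.51 × 0.00555/0.0225 = 3.59.

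Both round up to 4 per arm.

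**Difference detectable with 90% power, 10 per arm, k = 0.05.** Solving for p1 gives 7.8 points at m = 95 and 8.5 at m = 80.75. The t version gives 7.9 and 8.5.

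**k that gives 90% with 10 per arm.** V must equal 9 × 0.0225/10.51 = 0.01927.
- m = 81: k² = (0.01927 − 0.00565)/0.2925 = 0.0466, so k = 0.216.
- m = 95: k² = (0.01927 − 0.00482)/0.2925 = 0.0494, so k = 0.222.

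The t version gives 0.215 and 0.221. Without the added cluster (the 1 in the formula), the values are 0.232 and 0.238.

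**Power across k, 30% v 45%, 10 per arm.**

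| k | m = 81 | m = 95 |
|---|---|---|
| 0.05 | >99.9% | >99.9% |
| 0.15 | 98% | 99% |
| 0.20 | 93% | 94% |
| 0.22 | 89% | 90% |
| 0.25 | 83% | 84% |
| 0.30 | 71% | 72% |

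**Other readings of the inputs.**
- Alpha divided by three for the three primary outcomes: still at least 99.9%.
- 0.05 as an absolute between-pharmacy SD: 99.2% to 99.5%.
- 0.05 as an intracluster correlation (ICC), through a design effect without small-sample correction: 80% to 81%. With a t reference on 18 degrees of freedom: 76% to 77%.
- A 15% relative difference (30% v 34.5%): 42% to 47%.
- Persistence among initiators only, as the Outcomes section words it, at the pilot's 85% initiation (80.75 × 0.85 = about 69 women): above 99.9%.

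None of these gives 90%. Two readings do come close. An ICC of 0.05 with persistence falling from 30% to 15% gives 90% to 91%, but contradicts both the stated k and the hypothesis. About 25 women analysed per pharmacy at k = 0.05 also gives 90%, but contradicts the stated cluster size.

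**The case against.** The strongest defence is that the mismatch is in the safe direction. If k is 0.05 as written, the trial has more power than claimed, and the 90% can be read loosely as a minimum. No change to the design follows. That stands as far as it goes, and it limits the point to the text. It does not make the paragraph coherent: on its own inputs 4 pharmacies per arm would do, so the paragraph does not explain the choice of 10.

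Several stronger readings are tempting, and the documents do not support them.
- A reader might infer that the trial is underpowered. That needs k above about 0.22, and the article gives no estimate of k for these pharmacies.
- A reader might infer that 0.05 is really an ICC, or that the range of typical k was misquoted. The text calls the quantity k throughout, the cited sources are not at hand, and an ICC of 0.05 does not yield 90% for 30% v 45%. It is fair to put this to the sponsor as a question only.
- A reader might take the restricted, stratified randomization as evidence against k = 0.05. It uses purchase volume and sub-county, and says nothing about whether persistence differs between pharmacies.
- A reader might see a conflict between the attrition allowance and counting lost women as failures. The 30% may already include losses. If instead 30% and 45% are rates among women retained, 15% loss gives 25.5% v 38.25%, and power at k = 0.216 with 95 women falls from 91% to 89%. That is too small to carry a finding.
- The article makes no claim that the design is robust to variation between pharmacies, so no such claim needs withdrawing.

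**Conclusion.** The concern holds as an internal inconsistency: the stated k, cluster size, rates and number of clusters do not produce the stated power. The gap is 90% claimed against about 99.99% computed, or equivalently k = 0.05 stated against about 0.22 implied. Either the power is understated or the k is not the one the design rests on, and the article does not let a reader decide between them.

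The result assumes 30% v 45%, two-sided alpha 0.05, equal cluster sizes and the usual unmatched coefficient-of-variation formula. It does not depend on whether 81 or 95 women per pharmacy are counted, and the t version and simulation agree. It is not a finding that the trial is too small.

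**What to change.** Keep 10 pharmacies per arm and 95 women per pharmacy. In the Sample size section:
1. State which between-pharmacy parameter and value the calculation actually used, including whether 0.05 is k or an ICC. This should come from the original calculation, not from solving backwards for the k that returns 90%.
2. Restate k and power so that they agree.
3. Show power over a range of k, such as 0.15 to 0.30, at one stated cluster size. The columns for 81 and 95 women should not be mixed.

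The cost is a text correction and a rerun of a short calculation. It needs no additional pharmacies, women or follow-up, and leaves the analysis unchanged.
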